However, despite their biomechanical effects, few randomised controlled trials have evaluated their clinical efficacy [28-30]. In 156 patients with medial knee OA, no significant effect of laterally wedged insoles on symptoms over 2 years was demonstrated, as compared to control insoles [28]. However, a significant reduction in non-steroidal anti-inflammatory drug intake and greater compliance was observed with laterally wedged insoles, leading the authors to conclude that the results favoured a beneficial effect of the intervention. A recent double-blind, randomized, crossover trial in 90 patients found no effect of 6 weeks of lateral wedge use on pain or [30]. The samples selected for these studies may partly explain the non-significant effect of laterally wedged insoles. Whilst patients demonstrated medial knee OA, selection criteria did not consider knee joint alignment. Significant effects are more likely in participants with evidence of varus malalignment, rather than in a diverse cohort where alignment is likely to range from valgus (in which lateral wedges could be detrimental) to neutral to varus.

As previously stated, it is also important to evaluate the effect of treatment on disease progression. Only one clinical trial has investigated the effect of lateral wedges on knee OA progression [29]. Using annual x-rays for two years, this study failed to show that lateral wedges slowed joint space narrowing over time compared to control insoles. This non-significant finding may relate to the use of relatively insensitive x-rays as a measure of disease progression, as well as to an inappropriate patient group and the use of a short rather than full length wedge. Given the paucity of data attesting to the structural effects of lateral wedges over time, further research is necessary using more sensitive methods of measuring disease progression such as magnetic resonance imaging. Furthermore, no study to date has evaluated the cost-effectiveness of lateral wedges.

The aim of this trial is to determine whether wearing lateral wedge insoles for 12 months improves pain, physical function and health-related quality of life, slows structural disease progression and is more cost-effective than control flat insoles in individuals with medial knee joint OA and varus malalignment.

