A number of secondary outcomes will be used (Table 1). The Western Ontario and McMaster Universities (WOMAC) Osteoarthritis Index is a disease-specific instrument widely used in clinical trials, outcomes research and epidemiological surveys. Its validity, reliability and responsiveness have been demonstrated in an extensive range of studies [39]. The WOMAC consists of 24 questions covering pain, stiffness and physical function. It provides a total score as well as scores for each subscale.

The Assessment of Quality of Life (AQoL) instrument is designed to measure health-related quality of life. It has 15 questions that cover five dimensions including illness, independent living, social relationships, physical senses and psychological wellbeing. The AQoL has strong psychometric properties and is more responsive than other widely-used scales including the Medical Outcomes Study 36-Item Short Form (SF-36) [40,41]. It produces a single utility index that ranges from -0.04 (worst possible health-related quality of life) to 1.00 (full health-related quality of life). A clinically important difference in health related quality of life can be defined as a change of 0.04 AQoL units [42]. Population norms have been calculated for the Australian population [42].

Habitual physical activity will be measured in two ways, one using a questionnaire and the second using a pedometer. The Physical Activity Scale for the Elderly (PASE) will be used to measure both the level and type of recreational and occupational physical activity undertaken by participants over the previous week. The PASE was developed and validated in samples of older adults (age 55+ years) [43]. A pedometer (HJ-005 Omron Healthcare, Japan) will be worn at the waist for a week on two occasions, once at the beginning and once at the end of the 12-month study to record the number of steps taken per day. Participants will be asked to wear the pedometer full time during their waking hours. Pedometers have been found to be a simple and inexpensive means to estimate physical activity levels [44,45]. It is recommended that at least three days of sampling are needed to accurately assess activity levels given differences between weekends and weekdays [46].

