The primary economic evaluation will take the form of a cost effectiveness study with a range of outcome measures including the incremental cost per extra person with a clinically significant improvement in pain, per extra person perceived to be recovered, and per extra quality adjusted life years (using the AQoL over 12 months). A social perspective on costs will be taken that includes resource use incurred both by health services and by the participant irrespective of the source of payment. The inclusion of time/productivity gains is controversial and the cost effectiveness ratios will be calculated with and without these indirect costs. All health care costs will be included, however, to reduce the impact of extreme values, if inpatient hospital costs are unrelated to knee OA they will be excluded. Standard methods of economic evaluation alongside a clinical trial [58] will be used to evaluate the differences in resource use and health outcomes over 12 months between groups. The statistical analysis of costs data will be similar to outcome data although adjustments for overdispersion may be necessary. Confidence intervals for incremental cost effectiveness will be calculated directly using non-parametric bootstrapping [59]. In addition we will calculate a cost effectiveness acceptability curve based for a range of hypothetical money values of outcomes [60]. This will be done using individual cost and outcome data over the 12 months or, if adjustments for imbalance at baseline are necessary, using regression analysis [61]. Hypothetical money values will be taken from the decision making literature but the trial will also ask patients in each arm of the trial their willingness to pay for the treatment prior to and after treatment. This will not only provide money values for the calculation of net benefits but also provide evidence on the influence of health experience on the value of health outcome to patients.

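### Bootstrap intervals are planned directly on cost-effectiveness ratios with no rule for an effect difference compatible with zero; the cost-per-QALY ratio is the most exposed

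*Protocol article*

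**What the plan says.** The economic paragraph of Statistical analysis (protocol article) sets out a cost-effectiveness study whose outcomes include "the incremental cost per extra person with a clinically significant improvement in pain, per extra person perceived to be recovered", and the cost per extra QALY from the AQoL over 12 months. It adds that "the cost effectiveness ratios will be calculated with and without these indirect costs". The interval method is then fixed: "Confidence intervals for incremental cost effectiveness will be calculated directly using non-parametric bootstrapping [59".

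Two further outputs follow. One is the acceptability curve: "In addition we will calculate a cost effectiveness acceptability curve based for a range of hypothetical money values of outcomes [60". The other comes from the willingness-to-pay questions put to patients: "This will not only provide money values for the calculation of net benefits". No confidence interval for net benefit is stated. Regression is offered in the curve's description only if baseline imbalance makes adjustment necessary.

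On utility, Outcome assessment says: "A clinically important difference in health related quality of life can be defined as a change of 0.04 AQoL units [42". It gives the range of the index but no SD. Participants are assessed at baseline and at 12 months. Sample size calculations rests on pain and cartilage volume; no economic outcome has a precision or power figure.

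**The concern.** A ratio jumps from plus to minus infinity as its denominator passes through zero. If bootstrap replicates of the effect difference fall on both sides of zero, putting the replicate ratios in order does not put the results in order of merit.

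As an illustration, a replicate that saves 200 and gains 0.02 QALY gives −200/0.02 = −10,000. A replicate that costs 200 more and loses 0.02 QALY gives 200/(−0.02) = −10,000. These are opposite conclusions with the same ratio. On the net-benefit scale at an illustrative 50,000 per QALY they are 50,000×0.02 + 200 = +1,200 and 50,000×(−0.02) − 200 = −1,200, which are clearly apart.

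When the effect difference is compatible with zero, the confidence set for the ratio is not a bounded interval, yet sorted replicates still yield two finite limits. A reader could take those limits at face value.

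**Working it through.** **What the plan itself supplies.** There is no economic precision figure to reproduce. The number per arm comes from the cartilage calculation, which does reproduce: 80 completers per arm (100 less 20%), difference 5.3 − 3 = 2.3, SD 5.2, two-sided 0.05 gives power 0.80.

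**Inputs for the QALY ratio.** From the article: important AQoL difference 0.04; two assessments; 100 per arm. Assumed: linear accrual, so the QALY difference is 0.04/2 = 0.02; AQoL SD 0.15 to 0.25 at both times; baseline-to-12-month correlation ρ 0.5 to 0.7.

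**Formulae.** With QALY = (baseline + 12-month utility)/2:

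- unadjusted SE = SD × √((2+2ρ)/4) × √(2/n)
- baseline-adjusted SE = SD × √((1−ρ²)/4) × √(2/n)
- share of replicates below zero when the observed difference is 0.02: Φ(−0.02/SE)

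For SD 0.20, ρ 0.6, n = 100: unadjusted SE = 0.0253 and Φ(−0.79) = 21%; adjusted SE = 0.0113 and Φ(−1.77) = 3.9%.

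| SD | ρ | Unadjusted share below 0 | Adjusted share below 0 |
|---|---|---|---|
| 0.15 | 0.5 | 13.8% | 1.5% |
| 0.15 | 0.7 | 15.3% | 0.4% |
| 0.20 | 0.5 | 20.7% | 5.1% |
| 0.20 | 0.7 | 22.2% | 2.4% |
| 0.25 | 0.5 | 25.7% | 9.6% |
| 0.25 | 0.7 | 27.0% | 5.7% |

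With n = 80 in the same formulae the ranges are 17 to 29% and 0.9 to 12%. With an observed difference of zero the share is 50%.

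The useful threshold is 2.5%: above it, the two-sided 95% interval for the effect includes zero and the ratio has no bounded 95% interval. Every unadjusted case passes it. At 100 per arm the adjusted cases fall on both sides.

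**Chance, over repeated trials, that the QALY-effect interval includes zero** (80 to 100 per arm, ρ 0.5 to 0.7, true QALY difference 0.02). Unadjusted: 63 to 72% at SD 0.10 and 87 to 90% at SD 0.20. Adjusted: 2 to 17% at SD 0.10, 25 to 51% at 0.15, 49 to 69% at 0.20 and 65 to 79% at 0.25.

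**Pain-responder ratio.** From Sample size calculations: mean reductions 2 and 0.5, SD of change 3. Taking a reduction of at least 2 as response (assumed cut-off, normal distribution), the rates are Φ(0) = 50% and Φ(−1.5/3) = 31%. With 100 per arm, SE = √((0.50×0.50 + 0.309×0.691)/100) = 0.068 and z = 0.191/0.068 = 2.81, so about 0.2% of replicates are at or below zero; with 80 per arm, about 0.6%. Two-proportion power is 79% and 70%, so the chance that the effect interval includes zero is about 21% and 30%.

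**Recovered-person ratio.** Not computable, as no rates are given.

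**Coverage by simulation** (assumed: cost difference 200, cost SD 1,500, 50,000 per QALY, 80 per arm, SD 0.15 to 0.25). The percentile interval for the ratio covered 97 to 98% at a QALY difference of 0.04 or 0.02 and 93 to 96% at 0.01. With a cost difference of 1,000 it covered 91% at 0.01. At zero effect the ratio is undefined. The net-benefit interval covered 94 to 95% throughout, including zero effect.

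**The case against.** The strongest reply is that the same paragraph already holds most of the remedy. An acceptability curve and net benefits do not break down at zero effect, and regression adjustment is available. That stands, and it makes the point a small one. What it leaves is that the only interval stated is on the ratio, and that nothing says when to withhold it.

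A second reply is that the article never says percentile limits, and that the type of bootstrap interval may be set out in a fuller document or in the cited method. This is fair as to detail. But the choice to bootstrap the ratio directly is stated, and a pair of limits on the ratio scale has this difficulty whichever variant is used.

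Several stronger readings are tempting, and the article does not support them:

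- *That no valid interval exists.* Simulated coverage with a non-zero effect was often near or above nominal. The failure is mainly one of boundedness and interpretation.
- *That a straddling effect is likely even at the important difference.* This depends on an SD and a correlation the article does not give. With baseline adjustment the 2.5% threshold is not always passed, and the pain-responder ratio at the planned effect is not in that position.
- *That earlier trials make a null effect the likely case.* Background says of the two-year trial that "no significant effect of laterally wedged insoles on symptoms over 2 years was demonstrated, as compared to control insoles". That is non-significance, not proof of no effect. It also reports lower anti-inflammatory drug intake with wedges and notes that participants were not selected on alignment, whereas this trial requires varus knees.
- *That a costly and harmful result would pass as favourable.* Differences in resource use and in health outcomes are to be evaluated between groups, so the sign of each should be visible.

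**Conclusion.** The point holds in a limited form. The plan fixes a direct bootstrap interval on ratios and has no rule for an effect difference compatible with zero, where such an interval is unbounded and mixes opposite conclusions. The exposure is greatest for cost per QALY because the trial was not sized on utility and a 12-month gain of 0.04, if it accrues linearly, is worth only half that in QALYs. Whether baseline adjustment is used matters more than the assumed SD or correlation: it moves the share of negative replicates from 14 to 27% down to 0.4 to 10%. All the QALY figures rest on the assumed SD, correlation and linear accrual. The change is desirable rather than essential, since the acceptability curve and net benefits are already planned.

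**What to change.** In the economic part of Statistical analysis:

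- Make incremental net monetary benefit the quantity for inference, with a bootstrap 95% interval at stated money values, including the willingness-to-pay figures already to be collected.
- Adjust the utility difference for baseline AQoL as a rule, not only if imbalance is seen.
- Show the cost-effectiveness plane beside the planned acceptability curve.
- Report each ratio as a point estimate, with an interval only when at least 97.5% of bootstrap replicates share the same sign of effect.

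The cost is wording only. The same data and the same bootstrap replicates serve, with the baseline adjustment applied within each replicate.

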### Outcome assessment

Participants will be assessed at baseline and at 12 months by an assessor blinded to group allocation. Outcome measures have been selected based on those recommended for clinical trials of knee OA [35,36]. In those with bilateral knee OA, only the most symptomatic knee will be assessed.

Age, gender, duration of knee OA symptoms, previous treatment, surgery and medication use for knee OA will be obtained by questionnaire. Radiographic disease severity will be assessed from the baseline x-ray using the Kellgren and Lawrence grading system [31]. Skyline knee x-rays performed in nonweightbearing at 20° knee flexion will also be obtained to assess severity of OA within the patellofemoral joint. X-rays will be evaluated according to osteophytes and joint space narrowing based on a 4 point scale [34].

The primary outcomes will be knee pain and knee cartilage volume (Table 1). Average knee pain in the past week will be self-assessed by an 11-point horizontal numeric rating scale with terminal descriptors of zero = no pain and 10 = worst pain possible. Such measurement has demonstrated reliability in OA [35].

**Table 1 T1:** Outcome measures

**Primary Outcomes**	**Measurement**
Average pain in the past week	11 point horizontal numeric rating scale (end descriptors of 0 = no pain and 10 = worst pain possible)
Medial tibial compartment cartilage volume	Magnetic resonance imaging

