### Sample size calculations

Our sample size of 200 ensures adequate power for the two principal endpoints of change in pain and change in knee cartilage volume. Assuming that lateral wedges result in a mean pain reduction of 2 on our numeric rating scale (the minimum clinically important difference to be detected in OA trials [49]), that control insoles have a small placebo effect of 0.5 and that there is a SD of change of 3 (based on our previous data evaluating conservative OA interventions [50,51]), 170 participants would be required in total to give 80% power (2 sided test, alpha = 0.05). We have previously demonstrated a reduction in pain of this magnitude with knee taping [50] and physiotherapy for knee OA [51].

The other major end point is rate of knee cartilage loss. We have previously shown that the rate of tibial cartilage loss is 5.3 +/- 5.2% per year in a cohort with knee OA [52]. We categorized OA participants into tertiles: cartilage loss <3% per annum, 3–8% per annum and > 8% per annum. We found a linear increase in the risk of undergoing a knee replacement within 4 years [53]. Participants who lost cartilage at the rate of 3–8% per annum had a 2.4 fold (0.4 to 12.2) increased risk of requiring a knee replacement compared to participants who lost cartilage at the rate of <3% per annum. Those with the highest rate of loss of knee cartilage (>8% per annum) had a 7.1 fold (1.4 to 36.5) increased risk of requiring a knee replacement. These data suggest that a clinically useful outcome with lateral wedges would be to reduce the rate of knee cartilage loss to <3% per annum. With 100 subjects in each arm of the study, we will have 80% power to show a difference between a 5.3 +/- 5.2% per year rate of cartilage loss in the control group [52] and a <3% rate of cartilage loss in the intervention group (2 sided test, alpha = 0.05). This also takes into account a 20% drop-out rate.

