### Statistical analysis

A blinded statistician will analyse the data. All analyses will be conducted on an intention-to-treat principle using all randomized participants. Missing data will be replaced by the last score carried forward. Demographic characteristics and baseline data will be summarised by descriptive statistics. For outcomes measured using an essentially continuous scale, differences in mean change from baseline to 12 months will be compared between groups using linear regression modelling adjusting for baseline levels of the outcome measure. For knee cartilage volume, bone area, age and gender will also be included as covariates [54,55]. Model assumptions will be checked by standard diagnostic plots [56]. Participant measures of perceived improvement following lateral wedges or flat insole treatments will be compared by calculating the relative risks and their 95% confidence intervals using log binomial regression [57].

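### For the acceptability curve, baseline adjustment depends on an undefined judgement of imbalance, although a QALY from two AQoL scores would depend heavily on the baseline score

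*Protocol article*

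**What the plan says.** The economic paragraph of Statistical analysis lists three effect measures for the cost-effectiveness ratios. One is the cost "per extra quality adjusted life years (using the AQoL over 12 months"). On uncertainty it says: "Confidence intervals for incremental cost effectiveness will be calculated directly using non-parametric bootstrapping". No adjustment is mentioned there. It then introduces the acceptability curve, which is to be built from each participant's own costs and outcomes, with one alternative: "if adjustments for imbalance at baseline are necessary, using regression analysis". It does not say what makes adjustment necessary or which covariates would enter.

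Two other places matter. Outcome assessment fixes the schedule: "Participants will be assessed at baseline and at 12 months by an assessor blinded to group allocation". The preceding paragraph of Statistical analysis compares change from baseline to 12 months in continuous outcomes by "linear regression modelling adjusting for baseline levels of the outcome measure", with no condition attached.

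**The concern.** Baseline adjustment is an unconditional rule for AQoL as a clinical outcome, but only an option for the acceptability curve that uses QALYs derived from the same AQoL scores. With only two utility measurements, the baseline score is likely to be a large component of each participant's QALY, so a chance difference between arms at entry passes into the QALY difference.

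A rule that adjusts only when imbalance seems to call for it has two faults. It lets the analysis be chosen after the data have been seen. It also treats imbalance as the only reason to adjust, although a prognostic baseline covariate improves precision even when the arms are balanced. At stake are the cost per QALY, its interval and the QALY-based acceptability curve.

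**Working it through.** The protocol gives no QALY figure, AQoL SD or AQoL correlation, so there is no stated result to reproduce.

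**Inputs from the protocol**
- AQoL at baseline (u0) and at 12 months (u12): Outcome assessment.
- Arm size n = 100: "With 100 subjects in each arm of the study" (Sample size calculations).
- Important AQoL difference 0.04: "A clinically important difference in health related quality of life can be defined as a change of 0.04 AQoL units" (Outcome assessment, AQoL paragraph).

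**Assumptions**
- The QALY is the two-point trapezium over one year.
- AQoL SD is 0.20 (range 0.15 to 0.25), equal at both times.
- The correlation rho between u0 and u12 is 0.5 to 0.7.

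**1. Weight of baseline.** QALY = (u0 + u12)/2 × 1 year. The arm difference is therefore 0.5·d0 + 0.5·d12, where d0 and d12 are the differences at the two times. The direct weight of d0 is 0.5. A 12-month gain of 0.04 is worth 0.5 × 0.04 = 0.02 QALY. A baseline difference of 0.04 contributes the same 0.02 QALY with no treatment effect.

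**2. Chance imbalance.** SE(d0) = SD × √(2/100).

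| Assumed SD | SE(d0) | Direct carry-over of one SE (half) | As share of 0.02 QALY | Chance that the direct carry-over is at least 0.02 QALY in either direction |
|---|---|---|---|---|
| 0.15 | 0.021 | 0.011 | 53% | 6% |
| 0.20 | 0.028 | 0.014 | 71% | 16% |
| 0.25 | 0.035 | 0.018 | 88% | 26% |

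**3. Indirect carry-over.** Given d0, the expected value of d12 includes rho·d0. The total expected carry-over is therefore 0.5(1 + rho)·d0, which is 0.75, 0.80 and 0.85 of d0 at rho = 0.5, 0.6 and 0.7. The table shows the direct half only and so understates the total.

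**4. Precision.** The unadjusted variance is proportional to 0.25(2 + 2rho), and the variance adjusted for u0 to 0.25(1 − rho²). The ratio of standard errors, unadjusted to adjusted, is √[2/(1 − rho)]:
- rho = 0.5: √4.00 = 2.00
- rho = 0.6: √5.00 = 2.24
- rho = 0.7: √6.67 = 2.58

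**5. Simulation check.** In 20,000 simulated trials (100 per arm, SD 0.20, rho 0.6, true 12-month effect 0.04, hence 0.02 QALY), both estimators averaged 0.020. The standard error was 0.025 unadjusted and 0.011 adjusted. The slope of the estimate on d0 was 0.80 unadjusted and about zero adjusted. Among trials with a baseline difference near 0.02, the unadjusted estimate averaged 0.035 and the adjusted one 0.019.

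**The case against.** **Scope.** The conditional clause describes how the acceptability curve is built. It does not say how the QALY difference itself is estimated. The sentence on the bootstrap interval is silent, and silence in a condensed article is not a stated choice. This stands. A reader might infer that the protocol fixes an unadjusted analysis for every QALY result, but the text does not go that far. The written fault is the conditional rule for the curve. The interval needs only to be brought into line with the corrected rule.

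**Adjustment may already be covered.** AQoL is a continuous outcome under the unconditional rule, and the protocol says that costs will be analysed much as outcomes are. But that rule concerns change from baseline to 12 months and is not extended to QALYs, and the remark about costs does not mention them. The later conditional clause would also be hard to explain if adjustment were already settled.

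**The formula is assumed.** This stands, and the weight of one half depends on it. If QALYs gained were defined from change, (u12 − u0)/2, the expected carry-over would be 0.5(rho − 1)·d0, which is smaller and opposite in sign. The remedy does not depend on the choice: once u0 is in the model, adding or subtracting a multiple of u0 to the outcome leaves the arm coefficient unchanged.

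**Bias.** A reader might infer that the economic result is biased. It is not: under randomisation the unadjusted estimate is unbiased over repeated trials, and the bootstrap interval already includes the variance due to chance imbalance.

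**Contrast with the clinical outcomes.** Not every clinical outcome is adjusted for baseline. Perceived improvement is compared by relative risks with no adjustment stated. The contrast is with continuous outcomes only.

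**Conclusion.** The point holds within a narrow scope. For the acceptability curve the protocol sets an unadjusted default, with regression as an option triggered by an undefined judgement of baseline imbalance, and it states no adjustment for the bootstrap interval. This sits badly beside its own unconditional rule for continuous outcomes.

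Under the trapezium and the assumed SDs, an ordinary one-standard-error imbalance moves the QALY difference directly by 53% to 88% of the gain that corresponds to the protocol's important AQoL difference. Leaving baseline AQoL out roughly doubles the standard error or more at the assumed correlations. These sizes rest on an unstated formula and on an SD and correlation that the documents do not give. The objection to a data-dependent rule needs none of them.

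The two economic measures based on counts of improved or recovered participants do not involve this formula, and no clinical result changes. It should be corrected, but it does not threaten the trial's primary conclusions.

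**What to change.** Delete the condition on imbalance. State that the QALY difference (or net benefit) is always estimated by regression on arm with baseline AQoL as a covariate. Refit that model within each bootstrap replicate, and use it for both the incremental cost-effectiveness interval and the acceptability curve. Kellgren and Lawrence grade, the stratification factor, may be added. State the QALY formula in the same place. The raw difference can be shown as description.

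The cost is a change of wording: baseline AQoL is already collected, and no assessment or participant is added.
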